### Outcomes

#### Primary outcome measure

The primary outcome is adherence to immunosuppressive treatments 1 year after transplantation (M12). To assess therapeutic adherence (compliance and persistence), a combination of two methods is recommended [12]. Accordingly, we will use the BAASIS (Basel Assessment of Adherence to Immunosuppressive Medication Scale) questionnaire and the health insurance data from the national health data system (SNDS). The BAASIS questionnaire [13] will be used 1 year after the transplantation (M12) (Additional file 3). This is a recognized questionnaire for assessing adherence to immunosuppressive therapy. It includes 4 questions to determine whether, in the last 4 weeks, the patient forgot to take, did not respect the taking schedule (to the nearest 2 h) or changed the dosage of their immunosuppressive treatment. A patient answering “yes” to one of the 4 questions will be treated as a non-adherent.

Using the SNDS health insurance data, we will verify that over the year following the transplantation, 100% of the days are covered by immunosuppressive drug possession by counting the number of tablets dispensed by the CP during this period (for hospitalization days, therapeutic adherence will be estimated at 100%). The SNDS health insurance data are described in Additional file 4.

To be considered as adherent, a patient must be assessed as an adherent on both criteria.

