
At the time of the M1, M3 and M12 medical consultations, the hospital pharmacist will meet with the patient again. To further involve the patient, a booklet will be issued upon discharge from the hospital in order to inform them of the anticipated dates for the pharmaceutical consultations. For patients hospitalized at M1, M3 or M12, consultations will be staggered over time: they will be performed at the time of the first medical consultation following the patient’s discharge. The hospital pharmacist will carry out a drug assessment, draw up a list of undesirable effects, ensure appropriate drug intake, collect any problems or questions reported by the patient and will ensure the persistence of the educational messages given during the pharmaceutical hospitalization interviews. Also, prior to the consultation, he/she will contact the CP to ensure that this latter is in possession of the medication. A summary of this exchange will be written in the patient’s medical file and presented to the physician immediately prior to the consultation (Additional file 2).

Due to the nature of the assessed intervention, blinding will not be possible for patients and the healthcare team.

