### Analysis

Data will be analysed according to a pre-established statistical analysis plan that will be finalized before locking the database. The results of the study will be reported in accordance with the guidelines of the CONSORT Statement extension for the stepped-wedge cluster randomized trials [9]. In accordance with act no. 2002-303 of 4 March 2002, if they request it, the participants will be informed of the results of the study.

Cluster characteristics will be reported using descriptive statistics as will be patient characteristics, which will be reported per arm.

The primary endpoint is binary: patients adhering to their immunosuppressive treatment or not (assessed using the BAASIS questionnaire and health insurance data 1 year after transplantation). It will be analysed using a mixed logistic regression model taking into account a period effect and a cluster random effect. It will also be analysed using a mixed model with an identity link function (still taking into account both time and clustering), thus allowing to estimate a risk difference. All included patients will be taken into account in the main analysis and considered in the group (control or experimental) corresponding to the period during which they have been included, whatever occurred. In case the BAASIS questionnaire is missing, we will consider health insurance data (SNDS data) only to specify whether a patient is adherent or not. Because health insurance data are routinely collected data for all French people, we do not expect any missing data. No subgroup analyses or adjusted analyses are planned.

Binary secondary endpoints (adhesion, graft survival at 1 and 3 years, appearance of HLA antibodies, presence of episodes of acute rejection) will be analysed using the same approach as that used for the primary endpoint. For continuous secondary criteria (knowledge of the patient, patient satisfaction, coefficient of variation of the dosages), a mixed linear model will be used taking into account a period effect and a cluster random effect.

Data will be analysed by statisticians from the CIC Centre INSERM 1415 using SAS or R software.

The cost-utility and cost-effectiveness analyses will follow the French guidelines for economic evaluation in health care.

After the data management of SNDS data by the EpiDclic Unit, the health-economic analysis will be performed by UEME. It will be performed using the following software: Excel, Stata and R.

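### The SNDS half of the primary outcome requires every day of the year to be covered but is measured by a yearly tablet count, so supply meant for after M12 can hide earlier gaps in both arms

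*Protocol article*

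**What the plan says.** Protocol article, Primary outcome measure: a patient is classified by BAASIS and by SNDS data, and "To be considered as adherent, a patient must be assessed as an adherent on both criteria".

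- **SNDS.** The window is the first post-transplant year ("we will verify that over the year following the transplantation"). The criterion and the method stand in one sentence: "100% of the days are covered by immunosuppressive drug possession by counting the number of tablets dispensed by the CP during this period". Hospital days are credited as fully adherent. Additional file 4, which is not shown, is said to describe the SNDS data.
- **BAASIS.** It asks at M12 whether, "in the last 4 weeks, the patient forgot to take, did not respect the taking schedule" or changed the dosage.
- **Missing BAASIS** (Analysis section): "In case the BAASIS questionnaire is missing, we will consider health insurance data (SNDS data) only".
- **Contact with the community pharmacy** (Control and intervention phase). In the PPP phase, "At the time of the M1, M3 and M12 medical consultations, the hospital pharmacist will meet with the patient again", and before the consultation "he/she will contact the CP to ensure that this latter is in possession of the medication". The Abstract gives the purpose of this contact as discussing the patient's adherence. Control patients receive usual care, and pharmacy activities already in place are kept.

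**The concern.** Covering 100% of days and dispensing enough tablets for the year are different measures. The first asks whether tablets were on hand each day. The second asks only whether the sum is large enough. The last dispensing before M12 will usually contain tablets for days after M12, and in a total these offset earlier days on which the patient had none. The threshold is 100%, so a few days of leftover supply can change a patient's class.

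At stake is the half of the endpoint that does not rest on self-report. BAASIS does not repair it, because a gap in month 5 lies outside a four-week recall. When BAASIS is missing, the count decides alone. The cost per additional adherent patient may inherit the same error.

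**Working it through.** The plan gives no fill length and no figure for this misclassification, so there is nothing of its own to reproduce. Fill lengths, hospital stays and gap lengths below are assumptions.

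**1. When a count hides a gap.** Let H be hospital days, N = 365 − H the days that tablets must cover, c the days actually covered and g = N − c the gap days. Let D be the days' worth of tablets dispensed in the window and L the days' worth left at M12. Every dispensed tablet is either used by M12 or left over, so D = c + L. The count calls the patient adherent if D ≥ N, that is c + L ≥ c + g, or L ≥ g. The day-level criterion fails whenever g > 0.

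**2. Probability with 30-day fills and L uniform on 0 to 30 days.** P(hidden) = (30 − g)/30.

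| Gap g (days) | P(hidden) | Simulated range* |
|---|---|---|
| 5 | 25/30 = 0.83 | 0.76–0.95 |
| 10 | 20/30 = 0.67 | 0.52–0.71 |
| 15 | 15/30 = 0.50 | 0.29–0.48 |
| 20 | 10/30 = 0.33 | not run |

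*28- and 30-day refills, discharge on day 10 to 30, one delayed refill. The formula lies slightly above this range at 15 days.

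**3. Dependence on fill length.** Take an initial stay H of 7 to 28 days and one gap g of 1 to 21 days, giving 22 × 21 = 462 combinations.

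- *30-day fills.* The twelfth fill falls on day H + 330 + g, inside the window if H + g ≤ 34. Then 12 × 30 = 360 ≥ 365 − H, so the patient is adherent by count. Otherwise 11 × 30 = 330, which is below 365 − 28 = 337. Hidden: 7 × 21 + (20 + 19 + … + 6) = 147 + 195 = 342, and 342/462 = 74%.
- *28-day fills.* The thirteenth fill falls on day H + 336 + g, inside the window if H + g ≤ 28. Then 13 × 28 = 364 ≥ 365 − H. Otherwise 12 × 28 = 336 < 337. Hidden: 21 + 20 + … + 1 = 231, and 231/462 = 50%.
- *90-day fills.* Four fills give 360 ≥ 365 − 7 = 358. Hidden: 100%.

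Day-level coverage calls none of these patients adherent.

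**4. One patient, routine refills only.** H = 20, 30-day fills from day 20, one 10-day gap mid-year. The twelfth fill is on day 20 + 330 + 10 = 360. The count gives (12 × 30 + 20)/365 = 380/365 = 104.1%: adherent. Day-level coverage is (365 − 10)/365 = 97.3%: not adherent. Supply left at M12 is 390 − 365 = 25 days, more than the 10-day gap.

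**5. What one extra late refill would do, in either arm.** Take 30-day fills from day 0, a 10-day gap and the last routine fill on day 340. The count is 360/365 = 98.6%: not adherent. Add a refill on day 358 and the count is 390/365 = 106.8%: adherent. Day-level coverage is 355/365 = 97.3% both times.

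**The case against.** **The criterion is already day-level.** The sentence speaks of days covered, and counting tablets may only be shorthand for how coverage is derived. It does not say that tablets are credited backwards or left uncut at M12. Additional file 4 or the statistical analysis plan may hold a dated algorithm. This stands as a possibility. But the article says only that the file describes the data, and the one method printed in the primary outcome definition is a count. Applied as written, it can pass a patient who fails the criterion in the same sentence, which is more than an omitted detail.

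**A reader might infer a bias towards PPP**, because the pharmacy contact near the close of the window is a trial procedure in that arm only. The documents do not support this as a finding:

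- The wording can be read as a check of the pharmacy's own stock, and the Abstract mentions discussing adherence. Neither mentions bringing a refill forward.
- The contact is tied to the M12 consultation, which has no fixed day and is postponed for patients then in hospital. It may fall after day 365.
- Control clusters may keep existing pharmacy activities.
- The probabilities under steps 2 and 3 concern routine refills and apply to both arms. With 90-day fills the count already hides every gap in that grid, so an extra refill adds nothing.

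Any one-arm size depends on a response rate that the documents do not give. For illustration, assume that 30% of patients have a gap, 26% of gaps are not already hidden (1 − 0.74, 30-day fills) and all pass BAASIS. The ceiling is then 0.30 × 0.26 = 7.8 points if every contact produces an early refill, and 0.078 × 0.20 = 1.6 points if one in five does.

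**A reader might also infer that tablets left after a dose reduction inflate PPP adherence.** This does not follow. Doses can change in either arm, the pharmacist's drug assessment is not said to change them, and leftover tablets are in the patient's possession.

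**Conclusion.** The point holds as a mismatch between criterion and method that affects both arms. The printed tablet count can score real gaps in possession as full adherence. With 30-day fills and a uniform leftover at M12, a 10-day gap is hidden about two-thirds of the time. Over gaps of 1 to 21 days the hidden share is 50%, 74% or 100% for 28-, 30- or 90-day fills. These figures rest on assumed fill lengths and hospital stays and on a single gap per patient. They are shares of patients with a gap, not of all patients, and how many have a gap is unknown. The BAASIS half limits the damage only for patients whom BAASIS itself classes as non-adherent. A difference favouring PPP is possible but not shown, and no size is claimed for it.

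**What to change.** Replace the tablet total in the primary outcome definition with day-by-day coverage from dispensing dates:

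- Carry each supply forward from its dispensing date at the daily dose in force, and credit no tablet to a day before it was dispensed.
- Count hospital days as covered, as now.
- Cut supply at M12, and call a day covered only if tablets were on hand that day.
- Take the daily dose from the same source in both arms.

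If Additional file 4 or the analysis plan already does this, it is enough to correct the sentence and refer to that algorithm.

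Keep the full one-year window. Closing it early would depart from the stated year and separate it from the M12 BAASIS. At most, add a sensitivity analysis that ignores dispensings made shortly before M12, with coverage judged only up to that point, identically in both arms.

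The cost is some programming and a revised sentence, settled before database lock. The inputs should not be new: restricting a count to one year already needs dispensing dates, and turning tablets into days already needs a daily dose. The downside is a lower observed adherence rate, so non-adherence may lie above the 30% and 20% used for the sample size.

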#### Secondary outcome measures

A series of secondary clinical outcomes will be assessed at M12: adherence to all chronic disease drugs assessed with the EvalOBS scale [14], knowledge of hygienic-dietary measures and methods of taking immunosuppressive drugs assessed by a 9-item questionnaire [15] specially created for the study (Additional file 5), occurrence of adverse effects (search for 6 known side effects: hypertension, diabetes, kidney failure, bacterial, viral or parasitic infections) and graft status (graft survival, resumption of dialysis for renal transplant patient, new transplantation, patient death, acute rejection episodes). Via the EvalObs visual scale, the patient has to answer the question “how did you take your treatment in the last month”. For this, he is given a graduated scale from 1 to 17 (1 = I did not take any medication; 17 = I took all the tablets). Below 14, adherence to treatment is considered unsatisfactory.

Patients, practitioners and CP satisfaction will also be assessed thanks to a 5-level Likert scale.

Three years after transplantation (M36), graft status will be reassessed. Moreover, at M36, the risk of potential rejection will also be evaluated thanks to the study of the coefficient of variation (CV) of calcineurin inhibitor dosage. A patient with a CV greater than 30% will be considered to be at higher risk of rejection [16].

Finally, for renal transplant patients, the presence of anti-HLA antibodies will be tested at M12 and M36.

This study also includes a number of secondary health-economic objectives. The efficiency of PPP implementation will be evaluated over 1 year, performing a cost-utility analysis and two cost-effectiveness analyses from the French Healthcare Insurance perspective. The cost-utility endpoint will be the cost per QALY gained at 12 months. Quality of life data will be collected using the validated French EQ5D-5L survey, administered at 0, 1, 3, 6, 9 and 12 months’ follow-up. These questionnaires will preferably be collected face-to-face during patient visits to the hospital for medical follow-up. Otherwise, they may be collected by phone. The cost-effectiveness endpoints will be the cost per additional adherent patient and the cost per additional first functional graft in living patients at 12 months. Hospital and ambulatory costs, transport expenses and sickness allowances will be valued over a 1-year period. These consumed resources will be collected by specific retrieval from the SNDS. The cost of the PPP will be obtained through a microcosting procedure. For this, the hospital pharmacist will have to time the interviews and consultations.

### Funding source and regulatory aspects

This study is funded by the French Ministry of Health (PREPS number 2018-0486). The Tours University Hospital is the sponsor and is in charge of all administrative measures. The ethics committee (CPP Ile de France III – Hospital Tarnier - Cochin) has approved the study for all centres (reference Am8642-1-3728). The French committee for data handling (CNIL) approved the study (number 920070 dated 29/07/2020). This trial was registered with ClinicalTrials.gov (number: NCT04295928 on March 5, 2020, Establishment of a Personalized Pharmaceutical Plan in Renal or Hepatic Transplant Patients). This protocol was drafted as per the guidelines of the SPIRIT checklist (Additional file 1).

In the event that the sponsor wishes to amend the protocol, a request for a substantive amendment will be drawn up by the sponsor and sent to the CPP for approval. Once the amendment has been approved by the CPP, it will be sent to all the investigators and can be implemented. The protocol will also be updated on ClinicalTrials.gov. At last, any deviations from the protocol will be fully documented using a breach report form.

### Data management

Health professionals with direct access will take all necessary precautions to ensure the confidentiality of information, particularly with regard to their identity and the results obtained. These persons, in the same way as the investigators themselves, are subject to professional secrecy.

For each patient who agrees to participate in the study, the investigator is provided with a follow-up notebook in which he records all the clinical and quality of life information required by the protocol. The investigator is responsible for the accuracy, quality and relevance of data entered. Each notebook is anonymised: data is coded with the first letter of the patient’s surname and first name and a number specific to the research (N1) corresponding to the order of inclusion of the patients.

A copy of these anonymised notebooks will be sent to the coordinating centre by secure mail. In the coordinating centre, a clinical research technician will enter data into the e-CRF.

Access to SNDS data requires patient identification data. After a favourable opinion from the CNIL, each investigating centre will transmit a table of identifying data to a trusted third party (independent of the coordinating investigator, the sponsor and the investigating centres) by a secure e-mail. This table will not contain any medical, pharmaceutical or paramedical data and will comply with a strict format standard. It will contain the patient code in the study (N1), the surname, the first name, the date of birth, the place of birth (postcode + town + country) and the sex. These data will make it possible to reconstitute the beneficiary’s SNDS identifier, used for extractions from the SNDS database. A new anonymous number (N2) will be created for each patient and the SNDS data will be transmitted by this new anonymous number to a secure project space. The trusted third party will send the patient number (N1)—anonymous number (N2) equivalence table to the Health-Economic Evaluation Unit (UEME) of the University Hospital of Tours. Then, the UEME will make the link between the clinical data collected specifically for the study and the SNDS data. The SNDS data will remain strictly on this project space, and no extraction will be performed.

### Analysis

Data will be analysed according to a pre-established statistical analysis plan that will be finalized before locking the database. The results of the study will be reported in accordance with the guidelines of the CONSORT Statement extension for the stepped-wedge cluster randomized trials [9]. In accordance with act no. 2002-303 of 4 March 2002, if they request it, the participants will be informed of the results of the study.

Cluster characteristics will be reported using descriptive statistics as will be patient characteristics, which will be reported per arm.

The primary endpoint is binary: patients adhering to their immunosuppressive treatment or not (assessed using the BAASIS questionnaire and health insurance data 1 year after transplantation). It will be analysed using a mixed logistic regression model taking into account a period effect and a cluster random effect. It will also be analysed using a mixed model with an identity link function (still taking into account both time and clustering), thus allowing to estimate a risk difference. All included patients will be taken into account in the main analysis and considered in the group (control or experimental) corresponding to the period during which they have been included, whatever occurred. In case the BAASIS questionnaire is missing, we will consider health insurance data (SNDS data) only to specify whether a patient is adherent or not. Because health insurance data are routinely collected data for all French people, we do not expect any missing data. No subgroup analyses or adjusted analyses are planned.

Binary secondary endpoints (adhesion, graft survival at 1 and 3 years, appearance of HLA antibodies, presence of episodes of acute rejection) will be analysed using the same approach as that used for the primary endpoint. For continuous secondary criteria (knowledge of the patient, patient satisfaction, coefficient of variation of the dosages), a mixed linear model will be used taking into account a period effect and a cluster random effect.

Data will be analysed by statisticians from the CIC Centre INSERM 1415 using SAS or R software.

The cost-utility and cost-effectiveness analyses will follow the French guidelines for economic evaluation in health care.

After the data management of SNDS data by the EpiDclic Unit, the health-economic analysis will be performed by UEME. It will be performed using the following software: Excel, Stata and R.

An initial analysis will be carried out once all M12 data will be collected. Then, another analysis will be carried out with the data collected 3 years after the transplant.

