## Methods/design

### Study design and randomization procedure

This study will be a stepped-wedge cluster randomized trial. Clusters will be 12 transplantation units. In cases where a hospital has both a kidney and liver transplant unit, these units will correspond to two clusters. However, if both kidney and liver transplant patients are managed within the same transplant unit, this latter unit will be considered as a single cluster. In a stepped-wedge trial, all centres start the study on the same day in the control phase. Then, one after the other, at regular time intervals, each cluster will switch to the intervention phase and remain there until the end of inclusions. During the control phase, the practices of the different centres will not be modified. During the intervention phase, the PPP will be deployed.

In order to gain power, there will be as many sequences (and therefore switch dates) as clusters, meaning that only one cluster at a time will switch from the control phase to the experimental phase. A 7-week transition period will take place at the beginning of all intervention phases, such that the intervention can be rolled out under optimal conditions. The clusters will all be randomized at the beginning of the study and cluster gatekeepers informed of the randomization result. Because some centres had to recruit staff to carry out the intervention phase, communication of the randomization result is mandatory. Randomization will be managed by the biostatistician of the study at the Clinical Investigation Centre (CIC) INSERM 1415. The patient recruitment period will last 23 months with a 3-year follow-up (Fig. 1).

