### Sample size calculation

Currently, non-adherence to immunosuppressive treatment is approximately 30% [4]. The objective of the intervention is to reduce this percentage by one-third, i.e. to 20%. Considering a stepped-wedge design with 12 sequences (one cluster per sequence) of fourteen 7-week periods (one of which is a transition period), with a mean number of 11 patients recruited per cluster-period, this provides a 90% power to the study, taking into account an intraclass correlation coefficient of 0.01. Consequently, the total number of patients needed is 1716 of whom 132 are expected to be included in a transition period. Sample size calculation has been done using the shiny cluster randomized calculator [10, 11].

According to the French regulatory Agency’s 2017 data, the 12 recruited clusters could in turn recruit 2461 patients over 23 months. Considering that 25% of transplanted patients will have at least one exclusion criterion, 1846 patients will be included over 23 months.

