**Fig. 2 Fig2:**
[figure not shown]
Diagram showing the course of the study

During the intervention phase, the hospital pharmacist will be in charge of admission and discharge medication reconciliation, 3 pharmaceutical interviews, therapeutic follow-up and communication with the CP. Moreover, he/she will conduct 3 pharmaceutical consultations with the outpatient 1 month (M1), 3 months (M3) and 12 months (M12) after transplantation. To standardize this intervention over the various hospitals, hospital pharmacists will receive a 2-day training in medication reconciliation procedures, pharmaceutical interviews and consultations and therapeutic follow-up by an experienced clinical pharmacist who is accredited by the SFPC. Investigators (i.e. hospital pharmacist) from each centre will be trained at the sponsor centre (Tours University Hospital). Support documents (e-learning, support sheet for conducting pharmaceutical interviews, pharmaceutical consultations, drug reconciliations, standard letters to the attending physician, immunosuppressive drugs tryptic, checklist for CP, etc.) will be given to the trained centre. Each document will have been previously adapted to the current practices of the trained centre and validated by the latter. This training will take place in the 7 weeks preceding the intervention phase.

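### The primary analysis sorts every patient into control or experimental by inclusion period, but the protocol contradicts itself on which side of the switch the 7-week transition falls

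*Protocol article*

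**What the plan says.** Five places in the protocol article bear on this.

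- **Analysis.** The main analysis of the primary endpoint takes all included patients, each "considered in the group (control or experimental) corresponding to the period during which they have been included, whatever occurred". Only two groups are named. The model has a period effect and a random cluster effect.
- **Study design and randomization procedure.** "A 7-week transition period will take place at the beginning of all intervention phases". The transition is therefore part of the intervention phase.
- **Control and intervention phase** (text after Fig. 2). On the pharmacists' 2-day training: "This training will take place in the 7 weeks preceding the intervention phase". The training weeks therefore fall before the intervention phase.
- **Trial status.** One centre is reported as being in a transition phase and doing its training, counted apart from the centres already in the intervention phase. The first centre entered the intervention phase on 11 January 2021, after a common start on 7 October 2020.
- **Sample size calculation.** The design is "12 sequences (one cluster per sequence) of fourteen 7-week periods (one of which is a transition period"). An average of 11 inclusions is planned for each cell of that layout. On the total, the section states that "the total number of patients needed is 1716 of whom 132 are expected to be included in a transition period". The stated power is 90% at an ICC of 0.01.

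No section says which group transition-period patients join, or that they are left out.

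**The concern.** The grouping rule depends on the label of the inclusion period, and the label of one period per cluster is disputed within the document. Two statisticians following the text could code all 12 transition cells in opposite ways. Under the design section's wording, patients included while the pharmacist is still being trained count as patients of the personalized pharmaceutical plan. Under the intervention section's wording, the same patients count as usual care.

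This matters more than their share of patients suggests. In a stepped-wedge analysis with period effects, the cells next to the switch carry much of the information on the treatment effect, so a coding error there is magnified. If the choice stays open, it could also be made after the data have been seen.

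**Working it through.** **Inputs from Sample size calculation:** non-adherence 30% against 20% (difference 0.10); 12 clusters, one per sequence; 14 periods, one of them a transition period; 11 patients per cluster-period; ICC 0.01.

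**Assumed, because not stated:** two-sided 5% test; full effect immediately after the transition; a fraction f of the full effect in transition cells, varied from 0 to 1.

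**1. Layout and counts.** Cluster k (k = 1 to 12) has k control periods, 1 transition period and 13 − k intervention periods.
- Control: 78 cells x 11 = 858 patients
- Transition: 12 cells x 11 = 132
- Intervention: 78 cells x 11 = 858
- Total: 12 x 14 x 11 = 1848, and 1848 − 132 = 1716

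So with 14 periods, 1716 is the number outside the transition cells. It cannot also contain the 132. The dates support 14 periods: 7 October 2020 to 28 August 2022 is 690 days, or 98.6 weeks, against 14 x 7 = 98. From the start to the first intervention entry is 96 days, or 13.7 weeks, which is about two periods: room for one control and one transition period.

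**2. Method.** Generalised least squares on cluster-period means, with fixed period effects and a random cluster effect. Total variance = (0.30 x 0.70 + 0.20 x 0.80)/2 = 0.185. Power = Φ(expected difference/SE − 1.96).

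**3. The plan's own 90%.**
- 13 periods, no transition cells (1716 patients): SE 0.0310, power 89.7%.
- 14 periods, transition cells kept and correctly coded: SE 0.0307, 0.10/0.0307 − 1.96 = 1.29, power 90.2%.
- 14 periods, transition cells dropped: SE 0.0338, 0.10/0.0338 − 1.96 = 1.00, power 84.2%.

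The 90% is thus reproduced only when no transition cells are dropped. The exception is a cluster autocorrelation close to 0 (90.8% at 0), which is not the stated model.

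**4. Effect of the coding.** When transition cells carry f of the effect, the expected estimate is 0.10 x [1 − 0.312(1 − f)] if they are coded experimental and 0.10 x [1 − 0.312f] if coded control. SE is 0.0307 in both.

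| f | Coded experimental: estimate, power | Coded control: estimate, power | Excluded: estimate, power |
|---|---|---|---|
| 0 | 0.069, 61% | 0.100, 90% | 0.100, 84% |
| 0.25 | 0.077, 70% | 0.092, 85% | 0.100, 84% |
| 0.5 | 0.084, 78% | 0.084, 78% | 0.100, 84% |
| 0.75 | 0.092, 85% | 0.077, 70% | 0.100, 84% |
| 1 | 0.100, 90% | 0.069, 61% | 0.100, 84% |

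With variance 0.25 x 0.75 = 0.1875 the estimates are the same and the extreme power is 60%.

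**5. Sensitivity.** At f = 0 with experimental coding, the loss is 23% at an ICC near 0, 28% at 0.005, 31% at 0.01, 34% at 0.02 and 39% at 0.1. In 500 simulated trials fitted with the planned mixed logistic model (f = 0, ICC about 0.01), the mean log odds ratio was 0.67 of its true value and power was 61%.

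**The case against.** The strongest reply is that the rule is clear once read with the design section: the transition opens the intervention phase, so its patients are experimental, as an intention-to-treat analysis would have it. The SAP, due before database lock, can supply the detail. Dilution is conservative and does not create a false positive. The zero-benefit case may also be far from the truth. The plan runs through the first year with consultations at 1, 3 and 12 months, and a patient included during a 7-week transition reaches month 3 after it has ended.

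Much of this stands. The direction is towards no effect, the benefit fraction is unknown, and keeping these patients is a recognised choice. What does not stand is the claim of clarity, because two other sections place the training weeks outside the intervention phase. An SAP that excluded these patients would contradict the article's all-patients rule, so this is more than a detail left for later.

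A reader might infer that the 132 belong to neither group, or that the sample size already sets them aside. The documents support neither. No section gives these patients a third status, and Sample size calculation words the 132 as part of the 1716 without mentioning exclusion. The arithmetic conflicts with that wording, but this shows an error in the total and does not establish an intention to exclude.

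**Conclusion.** The point holds as a contradiction about where the transition sits, which the primary analysis rule does not resolve. Depending on the reading and on the unknown benefit fraction, the expected estimate lies between 6.9 and 10 points for a true 10, with power from about 60% to 90%. This rests on the protocol's planning values, an ICC of 0.01, a two-sided 5% test and a full effect straight after the transition.

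It would be wrong to read this as a 30% loss to be expected: 31% is the extreme in which transition patients gain nothing and are coded experimental, or gain everything and are coded control. At half benefit either coding loses 16%. Exclusion is the only one of the three options that is unbiased whatever the fraction. It has a price, since power is then about 84%, below the stated 90%.

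**What to change.** Before database lock:

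1. Reconcile Study design, Sample size calculation, Control and intervention phase, Analysis and Trial status on where the transition sits relative to the intervention phase. The sponsor must settle which description is right.
2. Amend the grouping rule in Analysis, for example: *Patients included during their cluster's 7-week transition period are excluded from the primary analysis. Sensitivity analyses include them, coded (a) as control and (b) as experimental.* The exclusion is set by cluster and calendar period, so it does not depend on what happens to a patient.
3. Restate the power for that analysis as about 84% with 11 patients per cluster-period. Holding 90% would take about 13.5 to 14 (89.8% and 90.7%).
4. Correct the total: 1848 patients over 14 periods, of whom 132 are in transition and 1716 remain for analysis.

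The text costs a few sentences. The substantive cost is a less favourable stated power and the loss of 132/1848 = 7.1% of patients from the main analysis; they remain in the sensitivity analyses.
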